### Primary outcome

We expect the proposed study to demonstrate that a unique intervention strategy can reduce disease activity and damage, as well as perceived and biological indicators of stress, while improving quality of life indicators in African-American lupus patients. This will result in changes (a) health behaviors (use of stress management techniques), (b) health status (quality of life, depression, perceived psychosocial stress, and disease activity), (c) health care utilization (hospitalizations, emergency room visits, and communication with physicians) and (d) biological markers (urinary catecholamines).

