### Quality of life

Quality of life will be assessed using two instruments that describe a spectrum of quality of life outcomes. The LUP-QOL incorporates the Medical Outcomes Study (MOS) Short Form 36 Health Survey (SF-36) and the Functional Assessment of Chronic Illness Therapy-Fatigue (FACIT-F), which are reliable and valid instruments that are frequently used in quality of life studies of persons with lupus [85–87]. The questionnaire includes questions pertaining to physical function, role function, social function, mental health, health perception and pain.

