### Neuroendocrine response to stress

Assessment of urinary catecholamine levels will require that the identified sub-sample of participants collect their own samples in a brown 24-h urine container with 30 mL 6 N hydrogen chloride (HCl) of urine collected and the date/time collection started and finished. Samples will need to be kept refrigerated between collections and then the completed container kept on ice until couriers pick up samples and bring them back to the lab for testing. Random subjects will be asked for an immediate additional collection to assess variability imposed by participant-specific factors. A 4–30 mL aliquot is necessary for analysis. Assessment of urinary catecholamines includes tests of urinary epinephrine, norepinephrine, and dopamine, which will be quantified using liquid chromatography/tandem mass spectrometry (LC/MS-MS) [88–90]. Once results are complete, they will be sent via Autofax.

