### Data analytic plan

#### Quantitative data analysis

Data will be entered immediately after specified collection points into an Excel worksheet that will be built upon after each collection point and imported into SAS for data manipulation. To minimize risks to confidentiality, all data will be de-identified by assigning a numeric code to each participant and labeling all materials corresponding to that participant with their unique identifier. Additionally, data files that include personal identifiers will be stored separately from signed consent forms in locked file cabinets that only the Principal Investigator will have access to. The basic experimental design and corresponding data analyses will represent a one-between subjects (intervention versus control and intervention versus set menu control) and one-within or repeated factor (pre, post, and follow up assessments) crossed factorial design, with multiple dependent outcome measures (disease activity and damage, perceived and biological indicators of stress, quality of life, and urine catecholamines). The multivariate (multiple qualitatively distinct measures at multiple times) approaches to repeated measures [95, 96], based on the general linear model or general linear mixed model, will be used to test for pre-post-follow up changes between the intervention group and the control groups, as well as for exploratory correlations with urine catecholamines. These approaches provide better description of longitudinal patterns for each dependent variable and they are easier to successfully implement and generally more powerful than the use of covariant models when multiple outcome measures are considered simultaneously [96]. *P* < 0.05 will be used to indicate statistical significance. The data from all randomized participants will be analyzed. Multiple imputations will be used to estimate missing data from dropouts and those participants who do not complete follow up evaluations. We will evaluate the first 12 months to address primary outcomes and exploratory analyses will be conducted after 12 months once participants are given the option to cross over. Basic descriptive statistics such as means, ranges, and standard deviations will be calculated and tabulated for quantitative data using SAS (SAS Institute, Cary, North Carolina). Project-specific frequencies and percentages will be presented as a recruitment diagram according to CONSORT guidelines.

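### The primary outcome is an unranked list of nine items, compared with two control arms at a flat 0.05, with no rule for which result makes the trial positive

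*Protocol article*

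**What the plan says.** The Primary outcome section gives four domains, with no item ranked above another:

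- "a) health behaviors (use of stress management techniques": one item.
- "b) health status (quality of life, depression, perceived psychosocial stress, and disease activity": four items.
- "c) health care utilization (hospitalizations, emergency room visits, and communication with physicians) and (d) biological markers (urinary catecholamines": three utilisation items and one biological item.

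The Quantitative data analysis section sets the comparisons as "one-between subjects (intervention versus control and intervention versus set menu control" and the threshold as "0.05 will be used to indicate statistical significance". It lists the dependent measures as "disease activity and damage, perceived and biological indicators of stress, quality of life, and urine catecholamines". It names a multivariate repeated-measures approach, based on a general linear or mixed model. It confines the primary evaluation to the first 12 months and makes later analyses exploratory.

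The Outcomes assessments section has urine catecholamines collected in a sub-sample of 50, at baseline and at the final 24-month evaluation only.

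**The concern.** A confirmatory trial needs a result, named in advance, that decides whether it succeeded. Here nine items share primary status, each can be set against two control arms, and the threshold is the same throughout. If the items are tested one by one, a programme with no effect has a substantial chance of producing a significant primary result somewhere. The headline outcome could then be chosen after the data are seen.

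The two lists make this worse. Health behaviours, depression and health care utilisation are primary in one section and absent from the dependent measures in the other. One primary domain, catecholamines, has no follow-up value inside the primary window. The article expects the project to inform policy and possibly standard care, so the choice of decisive result matters.

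**Working it through.** **Inputs from the protocol article**

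- Items in the Primary outcome section: 1 + 4 + 3 + 1 = 9.
- Items measurable in the first 12 months: 9 − 1 (catecholamines, baseline and month 24 only) = 8.
- Contrasts: 2, sharing the intervention arm; 50 planned per arm.
- Threshold: 0.05 per test.

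**Assumed, because the article does not give it**

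- Two-sided tests.
- One test per item per contrast.
- A common correlation ρ between outcomes, varied from 0 to 0.7.
- No true effect on any outcome.

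The article states no overall error rate, so there is no figure of its own to reproduce.

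**Step 1: simple bound.** Tests: 8 × 2 = 16. Expected false positives: 16 × 0.05 = 0.8. If all 16 were independent, the chance of at least one would be 1 − 0.95^16 = 0.56.

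**Step 2: shared arm and correlated outcomes.** I used 400,000 simulated trials with three equal arms and z statistics z₁ = (A − B)/√2 and z₂ = (A − C)/√2 for each outcome. A trial counts if any |z| exceeds 1.96. The last column counts only results that favour the intervention.

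| ρ | Any false positive, 8 items | Favouring the intervention only |
|---|---|---|
| 0 | 53.3% | 31.0% |
| 0.3 | 48.2% | 25.4% |
| 0.5 | 41.3% | 21.1% |
| 0.7 | 32.3% | 16.3% |

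**Step 3: joint-test reading.** If a single multivariate test at 0.05 gated each contrast, two tests would remain. With independence, 1 − 0.95² = 0.0975. For one outcome with two contrasts and the shared arm, simulation gives about 0.09. So this reading gives about 9% to 10%.

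**Step 4: the two lists side by side**

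| Item | Primary outcome section | Dependent measures in the analysis section |
|---|---|---|
| Health behaviours | yes, (a) | no |
| Depression | yes, (b) | not named |
| Utilisation (three items) | yes, (c) | no |
| Quality of life, stress, disease activity | yes, (b) | yes |
| Catecholamines | yes, (d) | yes, but no value inside 12 months |
| Damage | opening sentence only, not in (a) to (d) | yes |

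**The case against.** The strongest reply is that the article does not say each outcome is tested separately. It names a multivariate approach and defends it for handling several outcomes together. On that reading the error rate is about 10%, not about half. This stands as a limit on the size of the problem. It does not remove it, because the article never says that a joint test must succeed before individual outcomes are claimed. It also praises the method for describing each variable, which points the other way. A joint 12-month test could not include catecholamines in any case.

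A reader might count at least 11 primary variables, because "Assessment of urinary catecholamines includes tests of urinary epinephrine, norepinephrine, and dopamine", and so arrive at about 49% to 65%. The documents do not support that count for the primary analysis, since none of the three analytes is measured after baseline within 12 months. The count of eight could still rise: "Quality of life will be assessed using two instruments that describe a spectrum of quality of life outcomes".

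A reader might also say that the analysis section introduces damage. It does not: damage appears in the opening sentence of the Primary outcome section and is missing only from items (a) to (d).

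Finally, multiplicity procedures are often left to an analysis plan, which is not shown here. The absence of a named adjustment method is therefore not the point. The point is what this text fixes: an unranked primary list, one flat threshold, and lists that disagree.

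**Conclusion.** The concern holds. As written, the trial has nine co-equal primary items, two contrasts and no rule for success, and its lists of primary and analysed measures conflict.

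The size depends on a choice the article leaves open. With separate two-sided tests of the eight items available at 12 months, the chance of at least one false positive is about 41% to 53% for assumed correlations of 0.5 to 0, and about 32% at 0.7. With one joint test per contrast it is about 9% to 10%, still near twice the stated level.

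It would go too far to say that an ineffective programme will probably yield a false claim of benefit. Counting only results in its favour, the range is about 21% to 31% for correlations of 0.5 to 0. The correlations are assumptions, and overlap among self-report scales makes the independent end the less plausible one.

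**What to change.** By dated amendment, before any comparative data are seen:

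1. Name one primary endpoint at 12 months. A specified LUP-QOL score is a natural candidate, since quality of life is in the trial's title. The amendment must say which score, because the article describes the LUP-QOL as incorporating the SF-36 and FACIT-F.
2. Test it in fixed sequence at two-sided 0.05, for example intervention against usual care first and then against set menu. This holds the overall error for the primary claim at 5%.
3. Make a short list, such as PHQ-9 and SLAQ, key secondary outcomes under Holm.
4. Treat the rest, including catecholamines, as exploratory, with confidence intervals and no significance claims.
5. Make the dependent measures in the Quantitative data analysis section match, and settle the status of damage.

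Other designs are defensible, including a joint test, provided the text says that it gates the claims and orders the two contrasts.

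The cost is wording in the protocol and analysis plan, an update to the registration, and the loss of confirmatory status for some outcomes. Timing matters: the Trial status section reports 153 participants randomised and 30 with all assessments complete.

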### Secondary outcome

Measures of psychosocial and neuroendocrine responses to stress and disease activity and damage indices are expected to be inversely related to participation in intervention activities. Indicators of quality of life are expected to be positively related to participation.

### Self-report measures

Standardized methods will be employed for measuring associated outcomes in a validated fashion. Multiple measures were chosen to assess the impact of the intervention on targeted outcomes and quality of life. The criteria for choosing instruments and techniques were that they have been previously validated (preferably in African American populations), represent key outcomes in one or more past studies of chronic conditions (preferably lupus), are relatively brief (no more than 50–60 questions total), and sensitive to change in the range of 0.2 effect size. Selected measurement instruments are described below. Depending on participant preference, questionnaires will be mailed (paper and electronic) or administered by telephone. All biological samples for analysis will be promptly processed in a Labcorp facility to ensure standardization of assessment.

### Psychosocial stress

Psychosocial stress will be assessed by the Arthritis Self-Efficacy Scale pain and other symptoms sub-scale [82], which consists of 11 items designed to measure confidence in one’s ability to manage the pain, fatigue, frustration, and other aspects of disease; it was reworded in previous investigations to reflect lupus rather than arthritis [39].

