
### Evidence based prevention programs

A large body of evidence has shown that health-promoting programs in stress management have been successful in helping people improve their health practices and related health conditions [25]. Based on reviews of scientific literature, investigators have suggested that therapeutic interventions should be proposed to reduce psychological distress to improve quality of life and possibly moderate the evolution of chronic and unpredictable diseases like SLE [32]. Cognitive-behavioral stress management (CBSM) techniques have resulted in short-term improvement in pain, psychological function, and perceived physical function among persons with SLE [27]. Additionally, psychoeducation [33] and graded aerobic exercise [34] have been shown to be useful in the management of fatigue. Programs designed to reduce stress levels of chronically ill patients have also included support therapy, lifestyle interventions incorporating elements of yoga or other similar disciplines, and mini-sessions on depression, adaptive coping strategies, and body image [27–29]. Although there is no generally accepted self-management program available for SLE [16], two programs that have been shown to be successful in improving conditions in patients with arthritis are the Arthritis Self- Management Program (ASMP) and the generic Chronic Disease Self-Management Program (CDSMP). Each program incorporates six weeks of peer led sessions ranging in disease-specific and more general self-help content. Arthritis self-management education delivered by small-group, home study, computer, and Internet modalities have demonstrated significant improvements in health distress, self-reported global health, and activity limitation, with trends toward improvement in self efficacy and mental stress management [31, 35–57].

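### Perceived psychosocial stress, a primary outcome component, is measured only by a self-efficacy scale, and disease damage is listed for analysis with no described instrument

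*Protocol article*

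**What the plan says.** The Primary outcome section opens with the expectation that the intervention will "reduce disease activity and damage, as well as perceived and biological indicators of stress" while improving quality of life. It then lists outcomes (a) to (d). Item (b), health status, has four components: quality of life, depression, perceived psychosocial stress and disease activity. Damage is not in the list.

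The Psychosocial stress section gives one instrument: "Psychosocial stress will be assessed by the Arthritis Self-Efficacy Scale pain and other symptoms sub-scale". It describes the sub-scale as "11 items designed to measure confidence" in handling symptoms, reworded for lupus.

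The Secondary outcome section states the direction: "Measures of psychosocial and neuroendocrine responses to stress and disease activity and damage indices are expected to be inversely related to participation in intervention activities". Study design repeats this.

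Quantitative data analysis names "multiple dependent outcome measures (disease activity and damage, perceived and biological indicators of stress", followed by quality of life and urine catecholamines.

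In the background section on evidence based prevention programs, self-management education is credited "with trends toward improvement in self efficacy and mental stress management".

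**The concern.** Self-efficacy is belief in one's ability to cope. Perceived stress is how burdened or strained a person feels. The two may be related, but a change in one is not a measurement of the other. If the plan is followed as written, a change in confidence will be reported as a change in perceived stress. Reducing perceived stress is one of the trial's stated aims, in both the Abstract and Study aims.

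The stated direction adds to the problem. A programme that works should raise confidence, whereas the hypothesis expects stress measures to fall as participation rises.

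Damage raises a different question. It is listed as a dependent variable, but the article describes nothing that would yield a damage score.

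**Working it through.** No arithmetic applies. The check traces each named outcome to an instrument and compares the expected directions.

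**Step 1. Which instrument measures perceived stress?** The instruments come from Outcomes assessments and from the measure sections that follow it.

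| Instrument | What the article says it covers |
|---|---|
| Arthritis Self-Efficacy Scale sub-scale | confidence in managing symptoms (labelled psychosocial stress) |
| PHQ-9 | depression |
| LUP-QOL | quality of life |
| SLAQ | self-reported disease activity |
| Stanford questionnaires | utilization, illness intrusiveness, use of stress management techniques |
| Urinary catecholamines | biological response to stress |

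None measures perceived stress. Using a stress management technique is a behaviour, and the Primary outcome section lists it separately under (a). Catecholamines are the biological indicator, listed under (d). So one of the four components of (b) has no measure of the construct it names.

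**Step 2. Does the direction fit?**
- Hypothesis (Secondary outcome): measures of psychosocial response to stress are inversely related to participation.
- Scale (Psychosocial stress): measures confidence.
- Benefit (Evidence based prevention programs): an improvement in self-efficacy is favourable, and it is listed apart from mental stress management.

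If a higher score means more confidence, the expected relation to participation is positive, opposite to the stated one. The article does not give the scoring direction; this reading follows from the word confidence. Reverse scoring would remove the conflict of sign but not the mismatch of construct, and none is described.

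**Step 3. Where is damage named, and where is it measured?**
- Named in four sections: Study design, Primary outcome (opening sentence only), Secondary outcome and Quantitative data analysis.
- Measured by none of the six entries in the table. Disease indices assigns the SLAQ to activity. It describes the SLAM only as the source of the SLAQ items, and the SLAM is itself an activity measure.

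**Step 4. Is this only the brevity of an article?** For stress, no: the article positively assigns an instrument, and that instrument measures something else. For damage, the Self-report measures section says that the selected instruments are described, and the description has none for damage. The full protocol is not shown, however, and could name one.

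**The case against.** The strongest reply is that the consequences are limited, and in several respects that is right.

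- **A rise in confidence would count as failure.** A reader might infer this from the inverse hypothesis. The documents do not support it. The hypothesis states a direction for a construct, not a scoring rule. Quantitative data analysis tests change between groups over time at P < 0.05, with no success rule based on sign. The authors also plainly regard better self-efficacy as favourable.
- **Damage is a headline aim that the trial cannot meet.** A reader might infer this from the opening sentence of the Primary outcome section. But damage is absent from the aim in the Abstract, from Study aims and from the (a) to (d) list. It is better seen as a term that does not match the operative list.
- **The mismatch can be expressed as shared variance between self-efficacy and stress.** The article gives no correlation, so any such figure would be assumed.
- **A stress scale could be added now.** Trial status reports 153 randomized and 30 with all assessments complete. Baseline assessment precedes randomization, so a new scale would have no baseline value. It would reach an unknown remainder of participants and could not inform the 12-month primary comparison.

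These points narrow the consequences and the remedy. They do not touch the core: a confidence scale carries the label of stress, and a listed dependent measure has no described instrument.

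**Conclusion.** The point holds in limited form. For perceived stress, the plan is wrong as written: one of the four health-status components of the primary outcome is assigned a scale that, by the article's own description, measures something else, and nothing else listed fills the gap. The stated inverse direction does not suit that scale, on the assumption that higher scores mean more confidence. The sub-scale may be a sound measure of self-efficacy; the fault lies in its label and expected direction.

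For damage, the fault is smaller: a term used in four sections, once as a dependent measure, has no described instrument and is missing from the operative outcome list. This rests on the article alone.

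**What to change.** Before any outcome analysis, and as a documented amendment:

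1. Relabel the outcome in the Psychosocial stress section as self-efficacy for managing pain and other symptoms. State an expected increase under the intervention and a positive relation to participation. Carry the new label into Primary outcome, Secondary outcome, Study design and Quantitative data analysis.
2. Make no claim about perceived stress from this scale.
3. For damage, name the instrument if the full protocol has one. Otherwise remove the term from Study design, Primary outcome, Secondary outcome and Quantitative data analysis, so that they agree with the (a) to (d) list.

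No new data are needed. The cost is more than editing: with 153 participants randomized, this is a change to a named primary outcome component during the trial, and it must be dated and reported as such. The trial also gives up its claim on perceived stress and, unless an instrument exists, on damage. The described data could not have supported either.
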